**Figure 2 figure2:**
[figure not shown]
SPIRIT (Standard Protocol Items: Recommendations for Interventional Trials)-style schematic of the COMPASS Study. The figure summarizes the sequence of study activities, including community entry, participant recruitment and enrollment, quantitative and qualitative data collection, data analysis, interpretation of findings, and dissemination of study results. Legend: T0 – Community entry, participant recruitment & enrolment; T1 – Data collection; T2 – Data collection and interpretation; T3 – Data analysis & dissemination. This figure was generated using an artificial intelligence tool (OpenAI DALL·E). Prompt used: “Create a simple SPIRIT-style schematic illustrating study flow for the COMPASS Study from community entry to dissemination.” Source link to the generated image [55]. AGYW: adolescent girls and young women; COM-B: Capability, Opportunity, Motivation-Behavior; FGD: focus group discussion; KII: key informant interview.

### Data Collection

Quantitative and qualitative data will be collected sequentially to capture individual-level, social, and structural factors influencing integrated LARC and LAI-PrEP service delivery. Acceptability of integrated services, our primary outcome, will be measured using structured questionnaires that include Likert-scale items assessing willingness to use, perceived suitability, and compatibility with existing norms and values. The questionnaire was developed using the COM-B model and the BCW [48,49] and includes domains assessing health behaviors and preferences, interest and intent to use LARC and LAI-PrEP, perceived acceptability, barriers and facilitators, likelihood to recommend, and behavioral readiness. Perceived acceptability will be assessed using three four-point Likert-scale items evaluating whether (1) LARC fits within participants’ personal, cultural, and social context; (2) participants feel comfortable using LAI-PrEP within the community; and (3) perceived social acceptability among peers. Responses will be scored from 1 (Strongly Disagree) to 4 (Strongly Agree), with higher scores indicating greater acceptability. A composite acceptability score will be calculated by summing responses across these items. For descriptive analyses, acceptability scores will also be categorized into higher and lower acceptability using the observed median composite score of the study as the threshold. Other questionnaire domains will be analyzed individually to characterize interest, preferences, behavioral readiness, and perceived barriers and facilitators to integrated LARC and LAI-PrEP services. The complete survey questionnaire has been provided in Multimedia Appendix 3. Structured questionnaires, discussion guides, and interview tools are designed to assess sociodemographic characteristics, reproductive health history, HIV prevention behaviors, knowledge, attitudes, and perceived barriers and facilitators. Table 2 summarizes the key study domains, data sources, and participant groups.

**Table 2 table2:** COMPASS study measures, data collection methods, and participant groups.

Domain or measure	Description or examples	Data source and method	Participants
Sociodemographic factors	Age, education, marital status, residence, employment status	Structured questionnaire	AGYW^a^
Reproductive and sexual health history	Parity, contraceptive use, fertility intentions, pregnancy history	Structured questionnaire	AGYW
HIV prevention behaviors	Partner communication about HIV prevention (PrEP)^b^, sexual debut, number of sexual partners, partner status, condom use and condomless sex, drug use before sex, recent STI^c^ diagnosis	Structured questionnaire	AGYW
Knowledge, attitudes, and perceptions	Understanding, acceptability, and preferences for LARC^d^ and LAI-PrEP^e^	Structured questionnaire; FGDs^f^	AGYW
Barriers and facilitators	Accessibility, cost, stigma, peer and partner influence, community norms	FGDs; IDIs^g^	AGYW, policymakers, health care providers, community leaders
Implementation context	Facility readiness, provider training, policy environment, supply chain	IDIs	Policymakers, providers
Behavior change strategies	Recommended messaging, delivery approaches, and community engagement preferences	FGDs; IDIs	AGYW, stakeholders

^a^AGYW: adolescent girls and young women.

^b^PrEP: preexposure prophylaxis.

^c^STI: sexually transmitted infection.

^d^LARC: long-acting reversible contraception.

^e^LAI-PrEP: long-acting injectable preexposure prophylaxis.

^f^FGD: focus group discussion.

^g^IDI: in-depth interviews.

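### The primary acceptability score adds a LARC item, a LAI-PrEP item and a peer item, so disagreement on LAI-PrEP can be offset and the score does not show joint acceptance

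*Protocol article*

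**What the plan says.** All of the scoring rule stands in the protocol article, Methods, Data Collection. The outcome is named first: "Acceptability of integrated services, our primary outcome, will be measured using structured questionnaires". Its content is then given as "Likert-scale items assessing willingness to use, perceived suitability, and compatibility with existing norms and values".

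The measurement is narrower: "Perceived acceptability will be assessed using three four-point Likert-scale items evaluating whether" LARC fits the participant's own setting, "participants feel comfortable using LAI-PrEP within the community", and "perceived social acceptability among peers". Each item is scored 1 to 4. The rule for combining them is "A composite acceptability score will be calculated by summing responses across these items". No weights and no minimum per item are given. For description, the total is split into higher and lower at the observed sample median. The remaining questionnaire domains are analysed one at a time, outside the composite.

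Three other places bear on the point:

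- **Data Analysis:** plans logistic models for high acceptability and for willingness to use the integrated services, and collapses Likert answers into agree versus disagree.
- **Sample Size and Sampling Procedures:** sizes the survey (up to 220) on an assumed 85% acceptability of LARC and LAI-PrEP.
- **Study Population:** limits entry to women who use LARC or are interested in it, and says that willingness to use LAI-PrEP is expected to vary.

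**The concern.** The named outcome concerns two products offered together, while the score is a compensatory sum of single answers. As described, one item is about LARC only, one is about LAI-PrEP only, and the third is about peers with no product named. High marks on LARC and peers can therefore cancel a low mark on LAI-PrEP, and the total does not show which happened.

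The entry rule makes this direction the more plausible one, because women favourable to LARC but not to LAI-PrEP are eligible by design. The same fault works in reverse for a woman who disagrees on LARC.

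Two mismatches add to it. Willingness to use is listed under the primary outcome but is not one of the summed items. The sample size rests on a proportion, whereas the composite is a total from 3 to 12 or a split at its own median. At stake is whether the primary result, and the predictors of high acceptability, can be read as evidence on integration rather than on LARC alone.

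**Working it through.** **1. The plan's own figure.** The formula is n = z²p(1−p)/d². The article gives p = 0.85 but neither d nor an allowance for non-response. Assuming 95% confidence and d = 0.05, n = 1.96² × 0.85 × 0.15 / 0.05² = 195.9, so 196. With an assumed 10% non-response, 196/0.90 = 218, close to 220. Without inflation, 220 corresponds to d = 1.96 × √(0.85 × 0.15/220) = 0.047. The figure is plausible, and it is a calculation for estimating a proportion.

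**2. What the sum allows.** Three items scored 1 to 4 give 4³ = 64 answer patterns with totals of 3 to 12. In the order LARC/LAI-PrEP/peer:

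- 3/3/3 = 9 (agrees with everything)
- 4/1/4 = 9 (strongly disagrees on LAI-PrEP)
- 4/2/4 = 10 (disagrees on LAI-PrEP, yet scores above the woman who agrees with everything)

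| Total at or above | Patterns | LAI-PrEP item ≤2 | LARC or LAI-PrEP item ≤2 |
|---|---|---|---|
| 8 | 32 | 9 | 17 |
| 9 | 20 | 4 | 8 |
| 10 | 10 | 1 | 2 |
| 11 | 4 | 0 | 0 |

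Disagreement on LAI-PrEP is therefore compatible with the higher class at any effective cut up to 10 (up to 9 for strong disagreement), and never at 11 or 12. The article does not say where a total equal to the median goes. If higher means strictly above the median, the median must be 9 or less for this to happen.

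**3. How often (illustration).** The documents give no item distributions. Assume independent items, with agreement split evenly between 3 and 4 and disagreement evenly between 1 and 2. At a cut of 9, four patterns with LAI-PrEP ≤2 qualify: 3/2/4, 4/1/4, 4/2/3 and 4/2/4. At 90/70/80% agreement (LARC/LAI-PrEP/peer), each has probability 0.45 × 0.5 × 0.40 = 0.09 among women who disagree on LAI-PrEP, so 4 × 0.09 = 36% of them are classed as higher. The higher group is 70.3% of the sample, so they form 0.30 × 0.36/0.703 = 15% of it. The other rows follow in the same way. At 85% on every item the median is 10 and only 4/2/4 qualifies: 0.425 × 0.5 × 0.425 = 9%.

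| Assumed agreement | Median | Disagreers classed higher (≥ / > median) | Share of higher group (≥ / > median) | Size of higher group (≥) | Agree on both products |
|---|---|---|---|---|---|
| 85/85/85 | 10 | 9% / 0% | 2% / 0% | 58% | 72% |
| 90/70/80 | 9 | 36% / 9% | 15% / 5% | 70% | 63% |
| 95/60/80 | 9 | 38% / 9% | 22% / 8% | 68% | 57% |
| 90/50/70 | 9 | 31% / 8% | 28% / 12% | 56% | 45% |

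**4. Sensitivity.** Let 30–70% of agreement be strong and 30–50% of disagreement be strong, with latent correlation from 0 to 0.4. The share of the higher group that disagrees on LAI-PrEP is then 0–6% (≥ median) or 0–2% (> median) at 85% on every item. At 95/60/75% it is 10–25% or 0–11%.

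**5. The split does not estimate a proportion.** In the table, joint agreement of 72% and of 45% gives higher groups of 58% and 56%. A cut at the sample's own median largely fixes the size of that group, apart from ties. Nor can the two single-product proportions replace the joint one: at 85% each, joint agreement may be anywhere from 0.85 + 0.85 − 1 = 70% to 85% (0.85² = 72% if independent).

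**The case against.** The strongest reply is that other analyses already cover integration. Data Analysis dichotomises Likert answers and models willingness to use the integrated services, and interest, preferences and readiness are analysed individually. The composite would not be the only evidence. This stands and lowers the stakes, but none of it commits to a joint LARC by LAI-PrEP result or changes how the primary outcome is scored.

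Four further limits also stand:

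- The LAI-PrEP item asks about comfort within the community. A reader might infer that a woman who disagrees rejects the product. The documents do not support that, since she may want it and fear stigma.
- A reader might infer that the LARC item must sit near its ceiling because of the entry rule. That rule concerns use or interest, the item concerns fit with context, and Study Setting describes stigma and cultural barriers at these sites. A ceiling is possible but not shown.
- The article gives the items in short form and the questionnaire is not shown, so the peer item may name both products or the integrated service. That would narrow the content gap but leave the summing compensatory.
- The only acceptability figure in the article is 85%, at which the misclassification is small. Table 1 also links the interest route to PrEP, so many entrants may favour both products.

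A reader might also conclude that the composite should be replaced. With data collection complete, that is debatable, and it is not needed. Agreement with two single-product items is itself still not a direct measure of accepting one combined service.

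**Conclusion.** The point holds in a limited form. The compensatory property is certain from the stated rule and affects the continuous total whatever the cut. Classing a woman who disagrees on LAI-PrEP as higher is possible at effective cuts up to 10 and impossible at 11 or 12. The frequency cannot be known from the documents: it is small if about 85% agree on every item, and can reach roughly a quarter of the higher group if LAI-PrEP comfort is much lower than LARC fit and ties count as higher. Those figures rest on assumed item distributions.

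It is also clear that neither the sum nor its median split delivers the proportion on which the sample size is based, and that willingness to use is named under the primary outcome but absent from the composite. The summed score alone should not be interpreted as acceptance of integration.

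**What to change.** Before analysis starts, and documented as a change made after data collection, the plan should:

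- prespecify the proportion who agree or strongly agree on both the LARC and the LAI-PrEP item, with a 95% CI;
- report the LARC by LAI-PrEP cross-table and the distributions of all three items;
- keep the composite as planned and report it alongside, stating that it does not by itself show acceptance of integration;
- if the questionnaire contains an item on willingness to use, or acceptability of, the integrated service, report that proportion as the direct measure.

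No new data are needed for the joint proportion, because both product items are part of the survey. With 220 women, and treating them as a simple random sample, a joint proportion of 72% would have a 95% CI of about ±1.96 × √(0.7225 × 0.2775/220) = ±5.9 percentage points. The cost is slightly more reporting and a joint figure that cannot exceed either single-product figure.

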### Sample Size and Sampling Procedures

The quantitative sample size of up to 220 AGYW was estimated using the Kish-Leslie formula [51], assuming an 85% acceptability of LARC and LAI-PrEP if these services were made available. This sample size enables robust estimation of preferences, attitudes, and willingness to use integrated services, while accounting for variability in uptake across the study population. Participants will be purposively selected from the three KCCA clinics to ensure representation across urban, suburban, and peri-urban settings. For FGDs, a subset of 30 AGYW who completed the quantitative survey will be selected using stratified purposive sampling to ensure diversity in age, LARC and PrEP experience, and socio-demographic characteristics. This approach will enable in-depth exploration of factors influencing uptake and adherence. KIs will also be purposively sampled to capture a wide range of perspectives, professional roles, and influence over reproductive health and HIV prevention services. This combined sampling approach ensures a comprehensive understanding of both individual-level experiences and community-level factors affecting the integration and uptake of LARC and LAI-PrEP among AGYW in Uganda.

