Logistic regression models will be used to identify predictors of high acceptability and willingness to use integrated LARC and LAI-PrEP services. Variables considered clinically or theoretically relevant, together with those demonstrating an association at the bivariate analysis stage (*P*<.20), will be considered for inclusion in the multivariable models. Potential confounders, including age, education, socioeconomic status, marital status, prior contraceptive use, and HIV prevention history, will be retained in the final models where appropriate, based on subject-matter knowledge and statistical significance. Multicollinearity among independent variables will be assessed using variance inflation factors (VIFs) and correlation matrices. Where scientifically justified, interaction effects (for example, between age group and prior contraceptive use) will be explored by including interaction terms in the regression models. Model fit and assumptions will be evaluated using appropriate diagnostic procedures, including goodness-of-fit tests and assessment of influential observations. Adjusted odds ratios (aORs) with 95% CIs will be reported, and statistical significance will be assessed at a 2-sided α level of .05. Comparative analyses using 2-tailed *t* tests or ANOVA will further explore differences in preferences and attitudes across subgroups, including younger (15-19 years) versus older (20-24 years) AGYW and rural versus urban participants. For clarity of interpretation, results will be presented in tables summarizing numerical data and key statistics, including odds ratios (ORs) and *P* values. They will be visually illustrated with bar charts, pie charts, and histograms. Clustered bar charts and box plots will be used to highlight subgroup differences and significant predictors. This combined descriptive, inferential, and visualization approach will provide a robust understanding of AGYW preferences and attitudes toward LARC and LAI-PrEP, identify key facilitators and barriers to their uptake, and reveal demographic and behavioral predictors of positive engagement with these prevention methods.

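### The only definition of higher acceptability is a descriptive split at the sample's own median, yet high acceptability is the outcome of a planned logistic model and cannot be set against the 85% planning value

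*Protocol article*

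**What the plan says.** All references are to the protocol article.

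- **Data Collection** names the primary outcome: "Acceptability of integrated services, our primary outcome, will be measured using structured questionnaires". It then describes the score: "Perceived acceptability will be assessed using three four-point Likert-scale items". On scoring: "Responses will be scored from 1 (Strongly Disagree) to 4 (Strongly Agree), with higher scores indicating greater acceptability". On the total: "A composite acceptability score will be calculated by summing responses across these items".
- The same section adds the split and its declared purpose: "For descriptive analyses, acceptability scores will also be categorized into higher and lower acceptability". The same sentence sets the cut, so that scores are "categorized into higher and lower acceptability using the observed median composite score of the study as the threshold". It does not say where a score equal to the median goes.
- **Data Analysis** states: "Logistic regression models will be used to identify predictors of high acceptability and willingness to use integrated LARC and LAI-PrEP services". It does not say how high acceptability is derived. Separately, it collapses Likert responses to categories such as agree and disagree for chi-square tests, and it reports frequencies, percentages, means and medians.
- **Sample Size and Sampling Procedures** bases the 220 on the Kish-Leslie formula, "assuming an 85% acceptability of LARC and LAI-PrEP if these services were made available".

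**The concern.** Three statements do not fit together. The split is introduced as descriptive, but it is the only rule in the article that turns the composite into two classes, and the regression for acceptability needs two classes. A reader must either assume that the median split is modelled, contrary to its stated purpose, or accept that the model's outcome is undefined.

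A median cut is also relative to the sample. It ranks women against each other and does not say whether they find the services acceptable, whereas the survey was sized for an absolute proportion. If the split is modelled, the odds ratios contrast women above and below this sample's median, at a cut that another sample would move, and the information in the 3-12 score is reduced to one bit.

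**Working it through.** **1. Sample-size figure.** Kish-Leslie: n = z²p(1−p)/d², with p = 0.85 and z = 1.96. The article gives neither d nor a non-response allowance, so 220 cannot be reproduced from its inputs alone.
- Assuming d = 0.05: n = 1.96² × 0.85 × 0.15 / 0.05² = 195.9, so 196. An assumed 10% non-response allowance gives 196/0.9 = 217.8, so 218.
- With d = 0.0472 and no allowance, n = 220.

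The 220 is therefore not shown to be wrong. What matters here is that p is an absolute proportion and so needs an absolute yes/no rule.

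**2. What a median cut fixes.** Three items scored 1-4 give sums from 3 to 12, only ten values, so ties at the median will be common. By the definition of a median, at most 50% of women score above it and at least 50% score at or above it, whatever their attitudes. If high means above the median, 85% is impossible. If high means at or above, 85% can arise only through heavy ties. This step needs no simulation.

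**3. Size under assumed distributions.** Simulation of three 1-4 items from a latent normal, n = 220, latent correlation 0.3 to 0.7. The item distributions (strongly disagree/disagree/agree/strongly agree) are assumptions, not figures from the article.

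| Item distribution (%) | Usual median | High if ≥ median | High if > median | Sum ≥ 9 |
|---|---|---|---|---|
| 5/10/45/40, mostly agree | 10 | 57-58% | 34-39% | 76-77% |
| 30/45/15/10, mostly disagree | 6 | 57-59% | 38-39% | 13-17% |
| 3/12/60/25 | 9 | 72-74% | 40-43% | 73-74% |
| 1/4/20/75, correlation 0.5 | 12 | 57% | 7% | 94% |

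The first two rows have opposite attitudes and nearly the same high share, while a fixed cut at 9 separates them clearly. At correlation 0.5 the tie rule alone moves the high share by 58 − 37 = 21 points in row 1 and 57 − 7 = 50 points in row 4.

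**4. Who is called lower.** In row 1 at correlations 0.3 to 0.5, about 25-31% of the lower group agreed with all three items if ties count as high, and about half if they do not. In row 3 the figures are 0% and 42-47%.

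**5. Power.** Assumed latent shift of 0.35 SD between groups of 88 and 132 (220 split 1:1.5), row 1 items, correlation 0.4, two-sided 0.05, 3,000 runs. A t test or Mann-Whitney test on the full score has about 85% power. A chi-square test on the median split has about 70%, under either tie rule.

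**6. A fixed cut and the 85%.** When each item has 85% agreement (row 1), the share agreeing on all three items is 66-69% at correlations 0.3 to 0.5, and the share with a sum of 9 or more is 76-77%. Neither equals 85%, so the planning value must be tied to a named quantity before any comparison. If 85% were seen in 220, that is 187 against 33, with a 95% CI half-width of 1.96 × √(0.85 × 0.15/220) = 4.7 points.

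**The case against.** The strongest reply is that the article keeps the full composite, calls the split descriptive, and plans item-level agree/disagree proportions, so absolute information on acceptability will be reported. That stands. A reader might infer that the primary outcome is replaced by the split, or that the share above the median is the headline acceptability rate. The article says neither.

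It can also be said that the logistic outcome need not be the median split. That stands too: identifying the two is an inference from the only definition given, and the full protocol or analysis plan may hold another. It does not remove the point, because the alternative reading leaves the model's outcome without a definition in this document. The agree/disagree collapse does not supply one, since it concerns Likert responses and chi-square tests, not the composite.

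Three further stronger readings are not supported.
- It is tempting to say that all the regression is compromised. The logistic models also cover willingness to use the services, which the median split does not touch.
- It is tempting to say that the model would only separate strong agreement from agreement. In the mostly agreeing scenario, about 70-75% of the lower group (about half under the other tie rule) disagreed with at least one item, so the contrast is mixed. Odds ratios from it remain a valid relative comparison within the sample.
- The power example shows the cost of splitting, not the power of a named planned test. For younger versus older women the article also plans t tests or ANOVA.

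**Conclusion.** The point holds as a should-fix. The descriptive label on the split and the logistic model for high acceptability must be reconciled: as written, either the label is breached or the outcome is undefined. A sample-median cut with no tie rule cannot estimate the absolute 85% on which the survey was sized. These conclusions follow from the text and from the definition of a median. The sizes (high share 57-59% or 34-39% for opposite attitudes; power about 85% down to 70%) rest on assumed item distributions, correlations and effect size, and would differ with other assumptions.

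**What to change.** Before analysis starts:

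1. In Data Analysis, replace logistic regression on high acceptability with ordinal (proportional-odds) or linear regression of the 3-12 composite. Keep any median split purely descriptive, and state where scores equal to the median go. The willingness model can stay as it is.
2. Report an absolute acceptability proportion with its 95% CI from a fixed, scale-anchored cut set in advance, for example a composite of 9 or more (an average of agree). State which quantity the 85% refers to before comparing the two.

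The cost is a few sentences of wording. The Results section says that data collection is complete and that analyses were still planned, so no new data are needed. The downside is that effects are then on the score or cumulative-odds scale, which is less familiar than an odds ratio for a yes/no outcome. The fixed cut is best used for estimation and not as the regression outcome: at 85% acceptance it would leave only about 33 women in the smaller class.
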